###### Procedure

2.4.2.2.3

LFP will be recorded from the DBS macroelectrodes targeting the NAc the second day after the lead implantation and for two days. The day after surgery is dedicated to the patient’ recovery. The exposure task is performed using a 15-inch screen for the display, and a button pad for the ratings, while the patient is sitting on a chair. The patient is free to rest as long as needed in between blocks of trials, and to stop the experiment at any time if distress or discomfort is too high.

###### Recordings

2.4.2.2.4

LFP are recorded bilaterally using definitive leads (directional leads 6172 ABBOTT), which have 8 platinum-iridium contacts: one full ring contact, then two contacts with equally spaced three segments then one last full ring contact. Contact dimensions are 1.29 mm in diameter, 1.5 mm in length, and contact spacing 0.5 mm. The signal is amplified and digitized at 2048 Hz using an electroencephalogram amplifier (Refa system; TMSi, Oldenzaal, Netherlands).

###### Analyses

2.4.2.2.5

Bipolar recordings are reconstructed by filtering from 1 to 200Hz and subtracting signals between adjacent contacts of the electrodes. An artifact detection procedure is applied to reject a portion of a signal contaminated by electrical or movement-related noise. Bipolar signals are then segmented in trials and the time-frequency maps are computed using the adaptive multitaper algorithm. The statistical differences in power between symptoms-related and neutral images are assessed using linear models, including the induced level of distress, the arousal, and the familiarity of the images as factors. Signal processing, visualization, and statistical analyses are performed using MNE-python and R software (63). The analysis of LFP recordings during the exposure task are used at the population level to assess the presence of symptoms-related activity in the NAc and its frequency signature. These recordings are also eventually used at the individual level to localize pathological activities within the NAc to identify the best parameters for the stimulation such as the stimulating contacts.

### Participant timeline

2.5

A detailed schedule for trial participants is presented in **Table 4**.

**Table 4 T4:** Detailed schedule for trial participants.

Assessment	*Visit(s) with the referring physician* (prior to the trial)	Eligibility Visit 1 -4 weeks	Enrollment Visit 2 Week 0	Preoperative Visit 3 weeks after Visit 2	Surgery 4 weeks after Visit 3	Postoperative Visits 5-29					End of trial Visit 30 24 months after surgery (+/- 1 week)	*Post-trial* At least every 3 months
						Every month (+/- 1 week)	Every 2 months (+/- 1 week)	3 months after surgery (+/- 1 week)	12 months after surgery (+/- 1 week)	23 months after surgery (+/- 1 week)		
Eligibility screen	**X**	**X**										
Informed consent for trial			**X**									
Care-taker informed consent for trial			**X**									
Informed surgical consent				**X**								
Neurosurgical examination			**X**	**X**	**X**		**X**					**X**
Psychiatric examination		**X**	**X**		**X**	**X**						**X**
Body Mass Index measurement		**X**	**X**	**X**	**X**	**X**	**X**	**X**	**X**	**X**	**X**	**X**
Serious Adverse Events monitoring				**X**	**X**	**X**	**X**	**X**	**X**	**X**	**X**	**X**
Anesthetic evaluation				**X**								
Biological tests				**X**	**X**							
MRI				**X**								
Deep brain stimulation surgery					**X**							
Postoperative CT					**X**							
The Eating Disorder Inventory 2				**X**				**X**	**X**	**X**		
Psychiatric Scales												
1. Hospital Anxiety and Depression Scale 2. Yale Brown Obsessive-Compulsive Scale 3. Scale for Suicide Ideation				**X**				**X**	**X**	**X**		
Neurocognitive Scales												
1. Montreal Cognitive Assessment 2. Delay Discounting Task 3. Wisconsin Card Ranking Test 4. Brixton Test 5. Trail Making Test A and B 6. Slip-of-action test 7. Habits vs Goal Directed Behavior test 8. Dubois Five Word Test 9. Rey/Taylor Figure				**X**				**X**	**X**	**X**		
Quality of life Scales												
1. SF-36 Quality of Life Questionnaire 2. Global Assessment of Functioning Scale				**X**				**X**	**X**	**X**		
Care-taker Scale												
1. Zarit Burden Inventory (to be completed by the care-taker)				**X**				**X**	**X**	**X**		
Pupillometry				**X**				**X**	**X**	**X**		

Patients are informed by their referring practitioner of the existence of the protocol and the surgical possibilities before the selection visit (so outside the trial itself). Patients eligible for inclusion are discussed at a multidisciplinary meeting attended by psychiatrists, psychologists, neurologists, neuroradiologists, and neurosurgeons. Referring practitioners work in reference centers for the management of anorexia nervosa: patients deemed clinically or psychologically unstable are not presented at the multidisciplinary consultation meeting. Only after a positive collegial opinion has been obtained from the multidisciplinary consultation meeting can patients undergo the inclusion visit.

Patients who meet the inclusion criteria and do not have exclusion criteria are informed about the protocol during the selection visit. The inclusion visit takes place at least 2 weeks after the protocol description: this is a mixed consultation necessarily associating a psychiatrist specialized in the management of eating disorders and a neurosurgeon specialized in DBS. The patient’s trusted person and/or his relatives is present during this consultation. During the inclusion visit, the patient is asked to give or not his consent to participate in the study. The necessary steps before a DBS surgery (anesthesia assessment, MRI, blood tests) and the first neurocognitive assessment are performed during the preoperative visit. The patient has at least three visits and 8 weeks between the selection visit and the surgery.

The duration of follow-up after patient inclusion is 24 months. The patient is followed up at least monthly by the referring physician. These visits are part of the patient’s routine care: their frequency can therefore be modulated according to the care required but can never be less than monthly. The minimal investigations conducted during these consultations are as follows: 1) structured psychiatric interview; 2) measurement of BMI; 3) collection of SAR; 4) verification of the functioning (impedance measurement in particular) of the neurostimulation using the appropriate equipment (Physician programming system, Apple™ Ipad Mini, ABBOTT).

Concurrently, the patient will attend bi-monthly consultations with the neurosurgeon. Specific investigations performed during these consultations include: 1) a complete clinical examination including general physical examination, detailed examination of scars by the neurosurgeon; 2) verification of the proper functioning of the neurostimulation.

DBS programming is performed during a mixed consultation involving a psychiatrist specializing in the management of eating disorders and a neurosurgeon specializing in DBS. This mixed consultation can replace a simple neurosurgical consultation.

The included subjects benefit from three postoperative neurocognitive assessments: an early one, which takes place 3 months after surgery, a late one, which takes place 12 months after surgery, and a final one, which takes place 23 months after surgery. These assessments repeat the same tests as those performed during the preoperative visit.

Patients can keep the neurostimulator at the end of the study if they wish. The team that implanted the neurostimulator, the GHU Paris Psychiatry and Neuroscience team, manages it at the end of the protocol. The GHU Paris Psychiatry and Neuroscience hospital bears the costs. It should be noted that patients can then benefit from the implantation of a rechargeable internal pulse generator, which reduces costs.

### Data collection and management

2.6

An electronic case report form (eCRF) is used (Redcap^©^ v10.6.11, Vanderbilt University). Data entry is performed by the study investigators and their collaborators on this eCRF, on password-protected computers. Data are collected at each follow-up consultation and each neurocognitive assessment (the preoperative one and the 3 postoperative). The data collected directly in the CRFs and considered as source data are notably summaries of structured interviews with the patient, summaries of physical examinations, including measurements of the BMI, and collections of SAR within the follow-up booklet by the patient and at each follow-up consultation.

Participants consent in writing to the statistical treatment and scientific publication of these data in strict anonymity. Consequently, they will only be identified by their identification code. The lead investigator will conserve a participant identification list that will be used only if records need to be identified. Files will be stored on a password-protected computer in accordance with local data protection law and will be handled in strict confidence.

Documents related to the study will be conserved for the legal duration of 15 years and archives will be kept in a locked room under the responsibility of the lead investigator. Data cannot be moved or destroyed without the authorization of the lead investigator.

### Security and adverse events

2.7

#### Data monitoring

2.7.1

A clinical research associate (CRA) appointed by the sponsor, the GHU Paris Psychiatry and Neuroscience, ensures that the research is carried out correctly, and that the data generated are documented, recorded, and reported, by the Standard Operating Procedures implemented within the Direction de la Recherche Clinique et de l’Innovation from the GHU Paris Psychiatrie et Neurosciences Sainte Anne and in compliance with Good Clinical Practice and the legislative and regulatory provisions in force. Quality control visits are conducted monthly by the CRA.

#### Adverse events

2.7.2

Adverse events are at the heart of this study since the primary endpoint is the proportion of SAR occurring in patients. Participants will be asked about SAR at every study visit. Each serious adverse event will be reported by the principal investigator to the study promotor. These serious adverse events will be monitored until their resolution. They may lead to discontinuation of the protocol.

### Statistical methods

2.8

#### Sample size

2.8.1

This is a pilot study and is not intended to evaluate the device’s effectiveness. The required number of participants was set at 12, following the Julious’s recommendations (64). Considering that seven patients out of sixteen presented serious adverse event(s) in one of the largest reported series to date, 12 patients should be enough to detect this effect size (28, 65).

#### Statistical analysis

2.8.2

Statistical analysis will be performed at the end of the follow-up of all patients. The statistical analysis will be made in the biometrics center of the GHU Paris Psychiatry and Neurosciences. Data will be analyzed using JMP software (Version 14.1.0; SAS Institute Inc, Cary, North Carolina, USA). All analyses will be realized with a two-sided type I error rate of 5%. Quantitative data will be described by means and medians, standard deviations and interquartile ranges. Nominal data will be depicted by percentages with two-sided 95% confidence intervals. Time-to-event (time-to-relapse) data will be plotted by the Kaplan-Meier method. The proportions of missing data will be calculated. Patient characteristics (eligibility criteria, demographics, history, data at inclusion) will be described and compared by center. Quantitative data will be compared using Student’s t-test for a single sample (paired t-test) or ANOVA for repeated measures or non-parametric tests (Wilcoxon in paired series) when the distribution remains skewed even after appropriate transformation (Tukey power scale). Categorical data (pre vs. post) will be compared using Chi-2 or Fisher’s exact tests and or McNemar’s test for repeated measures.

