**Methods and analysis:**

This is a prospective, multicentre, single-arm, open-label, non-randomized pilot trial of bilateral nucleus accumbens deep brain stimulation for severe and enduring AN. Patients will be followed up for 24 months after deep brain stimulation. The main objective of this study is to measure the safety and feasibility of nucleus accumbens deep brain stimulation in this population. The recruitment rate will be collected prospectively. Potential deep brain stimulation efficacy will be monitored by changes in: 1) health-related quality of life; 2) weight; 3) eating disorder symptomatology; 4) neuropsychological changes of cognitive flexibility, habits formation, emotional processing and central coherence; 5) psychiatric comorbidities (anxiety, depression, obsession). Local field potential recordings during an exposure task will be proposed to the patients. Additionally, caregiver quality of life will be assessed.

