**Discussion:**

We present the design and rationale for a pilot study investigating the safety of nucleus accumbens deep brain stimulation for treatment resistant anorexia nervosa. This trial will provide an estimated effect size of nucleus accumbens deep brain stimulation for treatment-resistant anorexia nervosa to support future larger-scale clinical trials.

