The strengths of this study are the use of a directional DBS system, the target chosen for AN purpose only, and the patient inclusion not during a severe relapse of their treatment-resistant AN. This will help to obtain the real effect size of NAc DBS for treatment-resistant AN.

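### The trial is offered as a source of the effect size of NAc DBS, but it yields an uncontrolled pre-post change in 12 patients, and intervals are planned only for nominal data

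*Protocol article*

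**What the plan says.** The design is a "prospective, multicentre, single-arm, open-label, non-randomized pilot trial" (Abstract, Methods and analysis). On size, section 2.8.1 states: "The required number of participants was set at 12". The same section says that the study "is not intended to evaluate the device’s effectiveness".

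Section 2.8.2 sets one level for everything: "All analyses will be realized with a two-sided type I error rate of 5" per cent. On testing: "Quantitative data will be compared using Student’s t-test for a single sample (paired t-test) or ANOVA for repeated measures", with a paired Wilcoxon test where skewness persists after transformation. On description: "Quantitative data will be described by means and medians, standard deviations and interquartile ranges". Two-sided 95% confidence intervals are assigned to nominal data. No main efficacy outcome or time point is named.

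Section 2.4.2.1 and Tables 3 and 4 list hospital stay, BMI and a large battery of scales and tasks. The battery is done before surgery and at 3, 12 and 23 months after it. Section 2.3 allows medical treatment to change during stimulation.

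Two places say what the trial will deliver. Abstract, Discussion: "This trial will provide an estimated effect size of nucleus accumbens deep brain stimulation", in support of larger trials. Section 3, last paragraph: "This will help to obtain the real effect size of NAc DBS for treatment-resistant AN".

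**The concern.** The statement of purpose in 2.8.1 and the effect-size statements in the Abstract and Discussion pull in different directions, and the design supports only the first. Without a comparator, a pre-post change mixes any DBS effect with regression to the mean, expectation under open-label treatment, and the medication changes that section 2.3 allows. The features from which the Discussion derives its claim (directional leads, a target chosen for anorexia nervosa, inclusion outside a severe relapse) do not supply a comparator.

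The analysis section also stresses the less useful output. For a pilot meant to inform a randomized trial, the useful result is the size of the change and its uncertainty. For quantitative outcomes the article names summaries and tests, and gives intervals to nominal data only. A reader left with a point estimate and a p-value from 12 patients could size the next trial on a figure that is compatible with no change at all.

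**Working it through.** **Inputs from the protocol article.** n = 12, one arm (2.8.1, Abstract). Two-sided 5% and paired tests (2.8.2). One preoperative and three postoperative assessments with the same battery (2.5, Table 4). Eleven EDI-2 dimensions and six picture categories with pupil diameter, valence and arousal (2.4.2.1). The article gives no efficacy effect size, SD or number of comparisons, so there is no efficacy figure to reproduce.

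**1. Precision of a mean paired change.** Half-width = t(0.975, 11)/√12 × SD of the change = 2.201/3.464 = 0.635 SD. This is also the smallest observed change, in observed SDs, that reaches p<0.05. With 10 completers (an assumption) the half-width is 0.715 SD.

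**2. Interval for an observed standardized change of 0.5** (illustrative). t = 0.5 × √12 = 1.73 on 11 df. Inverting the noncentral t distribution gives a 95% CI of -0.11 to 1.09.

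**3. Number of tests.** The article does not state it, so this is a range under stated assumptions. Hospital stay and BMI count once each. Body composition and resting energy expenditure are left out.

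| Counting rule (cumulative) | Scores | Scores × 3 visits + 2 |
|---|---|---|
| One total per instrument, Trail Making A and B separate, pupillometry as one | 18 | 56 |
| 11 EDI-2 dimensions and 2 HADS scores | 29 | 89 |
| 8 SF-36 scales (assumption) | 36 | 110 |
| 6 pupillometry categories | 41 | 125 |
| Diameter, valence and arousal per category | 53 | 161 |

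With one repeated-measures ANOVA per outcome, which 2.8.2 also allows, the count is 18 + 2 = 20 at the low end and 53 + 2 = 55 at the high end.

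**4. Expected false positives if nothing changes.** Tests × 0.05: 20 give 1.0, 56 give 2.8, 100 give 5.0, 161 give 8.05. This expectation does not depend on correlation, but the chance of at least one false positive does:

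| Tests | Independent | Correlation 0.3 | 0.5 | 0.7 |
|---|---|---|---|---|
| 20 | 64% | 54% | 42% | 29% |
| 100 | 99.4% | 94% | 78% | 50% |

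The independent column is 1 - 0.95^k. The others are simulated with equally correlated normal statistics.

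**5. Exaggeration if only results with p<0.05 are carried forward** (simulation, n = 12, 300,000 trials per row; the true values are assumptions).

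| True change (SD) | Power | Mean standardized change among significant results | Ratio to truth |
|---|---|---|---|
| 0.3 | 16% | 0.85 | 2.8 |
| 0.5 | 35% | 0.90 | 1.8 |
| 0.8 | 71% | 1.03 | 1.28 |
| 1.0 | 88% | 1.15 | 1.15 |

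On the raw scale the ratios are 2.3, 1.6, 1.16 and 1.06. Required sample size varies as 1/d². A trial sized directly on the selected standardized figure would therefore be too small by a factor of about 2.8² = 7.8 at a true 0.3 SD, 1.8² = 3.2 at 0.5 SD and 1.15² = 1.3 at 1.0 SD.

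**The case against.** The strongest reply has three parts.

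First, this is a condensed article. A full protocol or analysis plan may add intervals for paired changes and a status for the p-values, and 2.8.2 does not exclude them. If the means and SDs are reported for change scores, a reader can compute the interval. This stands to the extent that the lack of an interval alone would be a weak finding. But 2.8.2 does say where intervals go, and no analysis plan can reconcile 2.8.1 with the effect-size statements.

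Second, section 3 openly names the single-arm, open-label design as the main limitation, and its later sentence says only that the trial will help to obtain the effect size. Estimating an effect without confirming efficacy is a normal aim for a pilot. This is fair as far as it goes, but the admitted limitation does not withdraw the claim. The claim attributes the size to NAc DBS, which an uncontrolled change cannot do.

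Third, a reader might infer that about 100 tests are planned, that several chance findings are near certain, and that every effect found will be strongly exaggerated. The document does not support these readings. It states no number of comparisons, and repeated-measures ANOVA brings the count down to about 20. The 99.4% figure is the chance of at least one false positive, not several, and it needs 100 independent tests with no true change. Scales completed repeatedly by the same 12 patients will be correlated. Exaggeration arises only from selection by p<0.05, which the document does not plan, and it is modest for true changes of 0.8 to 1.0 SD.

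**Conclusion.** The point holds as a mismatch between the promised result and what the design and planned summaries can provide. The article disclaims evaluating effectiveness, yet presents the trial as a source of the effect size of NAc DBS. What it will produce is an uncontrolled pre-post change with a 95% CI half-width of 0.635 SD of the change if all 12 patients contribute, and for quantitative outcomes that interval is not among the listed outputs. This rests only on n = 12, the single arm and the paired analysis.

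Multiplicity is secondary. About 1 to 8 false positives are expected if nothing changes, depending on how outcomes are counted. Whether to adjust for this in a pilot is a trade-off and is not pressed here. The exaggeration is conditional on selection by significance: about 2.8-fold at a true 0.3 SD, 1.8-fold at 0.5 SD and 1.15- to 1.3-fold at 0.8 to 1.0 SD. The document gives no value for the true change, so no single factor should be quoted as the expected one.

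**What to change.** In section 2.8.2, state that each quantitative efficacy outcome will be reported as the mean (or median) paired change with its 95% CI, for all outcomes whether or not they reach significance. Label p-values as unadjusted and descriptive, and state that no efficacy claim will rest on p<0.05.

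In the Abstract (Discussion) and the last paragraph of section 3, replace the effect-size claim with an uncontrolled pre-post change with its 95% CI, not attributable to DBS alone. The new wording is needed as well as the intervals, because an interval shows imprecision but does not remove the confounding from the missing control.

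The cost is a change of wording. The intervals come from the paired analyses already planned, with no extra patients, data or multiplicity adjustment. The downside is a less favourable stated claim.

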#### Primary endpoint

2.4.1

The primary endpoint is the proportion of serious adverse reactions (SAR) occurring in the patients included in the study. For continuous safety monitoring, we adopt a binomial sequential test, re-evaluated with each new patient, with the following parameters: maximum proportion of patients with SAR 15%, bilateral alpha 15%, beta 20%. The maximum and minimum tolerance limits for SAR were determined using the toxbdry function of the clinfun package version 1.0.15 of R. Taking the lower limit as a precaution, **Table 2** summarizes the maximum number of patients with a tolerable SAR to respect a threshold below 15%. This study design is justified because complications directly related to surgery typically appear within the first month (43). There are long-term complications of DBS which are taken into account in the protocol as the patients are followed up (44). These long-term complications must be put into perspective with the risk of death associated with SE-AN (2). The first three patients will be included sequentially with an interval of at least one month to ensure that there are no systematic adverse effects. If the 15% threshold of SAR in the study population is exceeded, as assessed in a sequential procedure, the study will be stopped.

**Table 2 T2:** Maximum number of patients with a serious adverse event to respect a threshold below 15%.

Number of included patients	Maximum limit of the interval
3	1
4	1
5	1
6	1
7	1
8	2
9	2
10	2
11	2
12	3

Highlighted numbers correspond to the maximum tolerated threshold of patient(s) presenting a serious adverse reaction related to the surgery (rounded down).

Serious adverse events are defined by the French National Agency for the Safety of Medicines and Health Products (ANSM) based on the French Public Health Code: “A serious adverse event is an adverse event that is lethal, or likely to be life-threatening, or leading to significant or lasting disability or incapacity, or causing or prolonging hospitalization, or manifesting itself as a congenital anomaly or malformation.”

SAR are serious adverse events directly caused by the intervention. In particular, we look for:

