## Discussion

3

Patients suffering from treatment-resistant AN have limited treatment options nowadays. They exhibit poor outcomes, even in expert centers (71). Our study protocol aims to support the growing literature on DBS for treatment-resistant AN.

Costs associated with AN are mostly related to hospital stays (72). The average length of stay for patients with AN is higher than 100 days in Europe (73). During hospitalization in expert centers, refeeding approaches lead to a clinical remission according to the BMI, even with higher-calory refeeding (74). However, relapse of AN arises frequently during the 18 months after hospitalization (75). This underlines the need to manage more community-oriented therapeutic approaches in AN patients. Our study does not require very low BMI to include the patient: the aim is more to manage the deinstitutionalization of AN patients than to obtain weight gain.

Whereas the safety of DBS is now well-established in neurological conditions, this question remains for treatment-resistant AN patients (76, 77). This study will help to refine the expected complication rate in front of these malnourished patients. Moreover, DBS is reversible and customizable. These two points explain why DBS, a reversible neuromodulation technique, should always be considered rather than irreversible lesion techniques (such as thermolesions, radiosurgery) in psychiatric patients.

The main limitations of this study are the single arm and open-label characteristics. This study design has been considered as mandatory by the French authorities. After confirmation of the DBS safety in patients with treatment-resistant AN, a larger study will be possible. The small study sample is in line with the main outcome of safety. We have decided to monitor the patient’s quality of life with two scales translated and validated in French, to minimize the common misgrading of quality of life in anorexia nervosa patients (78). However, these scales are generic and an eating disorder-specific measure would represent a nice to further studies (79). The measurement of healthcare intervention acceptability should investigate multiple aspects: despite numerous psychiatric follow-up visits, only limited data will be collected during the protocol (62). The development of a specific theory-informed questionnaire about DBS for SE-AN would have been a significant improvement and should be done for the next studies (80, 81).

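### The primary SAR proportion can stop early only for high counts, yet the stated reporting rule makes no allowance for this, so the raw percentage tends to overstate the true rate

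*Protocol article*

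**What the plan says.** Section 2.4.1 (Primary endpoint) of the protocol article: "The primary endpoint is the proportion of serious adverse reactions (SAR) occurring in the patients included in the study". On monitoring it says: "For continuous safety monitoring, we adopt a binomial sequential test, re-evaluated with each new patient". Table 2 gives the largest tolerated number of patients with a SAR: 1 for 3 to 7 patients, 2 for 8 to 11, and 3 for 12. The consequence of crossing is: "If the 15% threshold of SAR in the study population is exceeded, as assessed in a sequential procedure, the study will be stopped". No early stop for a low count is described.

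Section 2.8.1 (Sample size) fixes the maximum: "The required number of participants was set at 12".

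Section 2.8.2 (Statistical analysis) has one general sentence on proportions: "Nominal data will be depicted by percentages with two-sided 95% confidence intervals". It names neither the interval method nor an estimator that allows for the stopping rule, and it does not set the primary endpoint apart.

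The Discussion gives the rate a use beyond monitoring: "This study will help to refine the expected complication rate in front of these malnourished patients".

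**The concern.** A raw proportion x/n is unbiased when n is fixed in advance. Here n depends on the data. A run of early SARs ends the study with a small denominator and a high percentage, while a run without SARs continues to 12 and can still be diluted or added to. High early values are frozen and low early values are not, so the average reported percentage lies above the true rate.

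The SAR rate is the trial's main result and is meant to inform the complication rate expected in a larger trial. A reader who takes the raw percentage after a stop at face value would plan on too high a rate, with nothing in the report to say so.

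**Working it through.** **Inputs.** Limits from Table 2; maximum 12 patients (section 2.8.1); report x/n (section 2.8.2). Assumptions: the study stops when the count exceeds the limit; looks start at 3 patients; each SAR is known before the next decision; x and n are frozen at the stop.

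**The plan's own figures.** Section 2.4.1 states a 15% limit, two-sided alpha 15% and beta 20%. Under the reading above, Table 2 stops with probability 33.1% at a true 15%. The second rate given to the boundary function is not printed, so the table cannot be rebuilt. That mismatch is a separate matter; the table is used here as printed.

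**Method.** There are 13 possible end points (n, x). Because of the steps in the table, a stop can occur only at n = 3 to 7 and 9 to 11. Let A(n, x) be the number of SAR sequences that reach an end point without an earlier stop. Then

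P(n, x) = A(n, x) · p^x · (1 − p)^(n − x), and mean reported rate = Σ P(n, x) · x/n.

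The unbiased estimator is A₁(n, x)/A(n, x), where A₁ counts those sequences whose first patient has a SAR.

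| End point x/n | A | A₁ | P at p = 15% | Raw % | Unbiased % |
|---|---|---|---|---|---|
| 2/3 | 3 | 2 | 0.0574 | 66.7 | 66.7 |
| 3/3 | 1 | 1 | 0.0034 | 100 | 100 |
| 2/4 | 3 | 1 | 0.0488 | 50.0 | 33.3 |
| 2/5 | 4 | 1 | 0.0553 | 40.0 | 25.0 |
| 2/6 | 5 | 1 | 0.0587 | 33.3 | 20.0 |
| 2/7 | 6 | 1 | 0.0599 | 28.6 | 16.7 |
| 3/9 | 7 | 1 | 0.0089 | 33.3 | 14.3 |
| 3/10 | 15 | 2 | 0.0162 | 30.0 | 13.3 |
| 3/11 | 24 | 3 | 0.0221 | 27.3 | 12.5 |
| 0/12 | 1 | 0 | 0.1422 | 0 | 0 |
| 1/12 | 12 | 1 | 0.3012 | 8.3 | 8.3 |
| 2/12 | 45 | 5 | 0.1993 | 16.7 | 11.1 |
| 3/12 | 34 | 4 | 0.0266 | 25.0 | 11.8 |

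The probabilities sum to 1. The mean is 41.9% among stopped trials and 9.7% among completed ones: 0.331 × 41.9% + 0.669 × 9.7% = 20.4%, which is 36% above the true 15%. The unbiased column averages to exactly 15.0%.

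**Other true rates, count frozen at the stop.**

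| True rate | Mean raw % | Relative excess |
|---|---|---|
| 2% | 2.2 | +9% |
| 5% | 6.0 | +20% |
| 10% | 13.1 | +31% |
| 15% | 20.4 | +36% |
| 20% | 27.3 | +36% |
| 25% | 33.6 | +34% |
| 30% | 39.2 | +31% |
| 43.75% (the 7/16 of section 2.8.1) | 52.3 | +19% |

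**Patients already included at the stop.** If 1, 2 or 3 further patients (total capped at 12) are still counted, each with the true risk, the mean at a true 15% is 18.7%, 17.6% or 16.8%, that is +24%, +17% or +12%.

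**Intervals.** Total miss rate of a 95% interval (nominal 5%):

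- Exact Clopper-Pearson: 0.3% at a true 15%; never above 4.3% at any rate.
- Wilson score: 11.0% at 15%, against 2.4% with a fixed 12 patients; 10.4% at 20%, against 1.9%. The 11.0% hangs on the lower limit for 2/4 being 15.004%; at a true 15.1% the miss is 6.2%.

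An exact interval for the sequential design, ordering outcomes by x/n, is 3.5% to 49.2% at 3/12, against 5.5% to 57.2% for Clopper-Pearson.

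**The case against.** **The analysis plan is not shown.** The sentence in section 2.8.2 is generic, and the choice of estimator after a sequential boundary often sits in the analysis plan. This limits the point but does not remove it. The article fixes both a one-sided stopping design and a reporting rule that covers the primary endpoint, and following that rule gives a biased estimate.

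**The size depends on freezing the count.** The final analysis comes after all follow-up, SARs are collected for 24 months, and only the first three patients are spaced by at least a month. Patients already implanted at a stop would stay in the denominator. This stands: an excess of about a third is the frozen-count case, and the overrun figures belong beside it.

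**The adjusted estimate has drawbacks for safety.** A study stopped at 3/9, 3/10 or 3/11 would show 14.3%, 13.3% or 12.5%, all below the 15% limit it had just crossed. At a true 25% the adjusted figure is 15% or less in about 44% of trials, against 16% for the raw one. Its root mean squared error is lower at a true 15% (0.158 against 0.190) but higher at 30% (0.233 against 0.228) and at 43.75% (0.268 against 0.228). Raw bias at least errs towards overstating harm. This also stands, and is why the adjusted figure should sit beside the raw one and not replace it.

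**Two stronger readings are tempting.** A reader might infer that the reported interval misses at more than twice its stated rate. The documents do not support this in general, because no interval is named, Clopper-Pearson holds its coverage, and the score interval fails only at some rates. A reader might also infer that the looks cause a true 10% rate to be reported above 15% in about a third of trials. The looks add nothing there: every stopped path has at least 2 SARs, so the event is simply 2 or more among 12, with probability 34.1% in a fixed design too.

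**Conclusion.** The point holds for the estimate. As written, the primary SAR percentage ignores a stopping rule that acts only on high counts, and it is biased upward. With Table 2 read as stopping above the limit and the count frozen there, the relative excess is about 31% to 36% for true rates of 10% to 30%. It is smaller outside that range and when patients already included are counted.

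At a true 15% the bias is about 5 percentage points against a root mean squared error of 19 points. It is therefore a correctable distortion in a small pilot, not a reason to doubt the design. For the interval, what can be said is that the method is unnamed and the choice matters. SARs that appear late in follow-up would change all these figures.

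**What to change.** In section 2.8.2, add for the primary endpoint:

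- the raw count and percentage of patients with a SAR, with an exact (Clopper-Pearson) 95% interval;
- beside it, an estimate and exact 95% interval that allow for the Table 2 boundary, for example the unbiased estimator for the sequential binomial design with stage-wise ordering of outcomes;
- a statement that the raw percentage is biased upward when the study stops early;
- how patients already included at a stop, and SARs found later, enter both figures.

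Show both figures when planning the larger trial. The stopping rule itself is untouched.

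The cost is a few sentences and a calculation over at most 13 outcomes (more if patients included after a stop are counted). The downside is one extra figure to explain, which can fall below 15% after a stop and is less precise at high true rates. The raw count stays visible, so no safety signal is hidden.
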